
#### Sample Size

We based sample size estimates on a two-tailed significance level (alpha) of .05 and power (1-beta) of .80 [96]. With 115 individuals in each arm (N=230), we would be able to detect even a 4% increase in adherence in the intervention arm. We expect a loss to follow-up rate between 8% and 10%, but conservatively account for a 15% loss to follow-up rate and increased our overall sample size target to 270. Power for this type of trial should be sufficient to identify small to moderate effects [97] (defined as effect sizes of 0.2-0.5 [98]). Even if we have a higher than expected loss to follow-up rate of 15%, we will have sufficient power to detect effect sizes of 0.35, well within the small-to-moderate effects continuum and in line with the magnitude of effects seen in other adherence intervention studies [44,99,100]. We expect several of our outcomes will be more responsive to change than overall adherence particularly many of the binary process outcomes. We will have more than sufficient power to detect differences in those outcomes. While we plan to attempt to enroll 270 individuals, one of the outcomes of interest is the willingness of patients to participate in these types of interventions. Therefore, we are also specifically interested in whether it is feasible to enroll this many individuals from a clinical care setting in a reasonable amount of time.

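### The stated inputs give 80% power for an effect size of 0.37 at 115 per arm, not for the 0.35 claimed after 15% loss (power there about 75%)

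*Protocol article*

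**What the plan says.** All the inputs are in the Sample Size section of the protocol article. The error rates come first: "We based sample size estimates on a two-tailed significance level (alpha) of .05 and power (1-beta) of .80". The required number follows: "With 115 individuals in each arm (N=230), we would be able to detect even a 4% increase in adherence in the intervention arm". The investigators expect to lose 8% to 10% but "conservatively account for a 15% loss to follow-up rate and increased our overall sample size target to 270". The standardized effect is then tied to that pessimistic case, with the statement that even at 15% loss "we will have sufficient power to detect effect sizes of 0.35".

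The Design section gives 1:1 allocation. The Statistical Analyses section says a linear mixed-effects model is likely, focuses the primary comparison on one year after enrollment, and leaves open whether baseline is handled by adjustment or by change scores. The Sample Size section gives no standard deviation, no correlation between baseline and follow-up, and no number of repeated measures.

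**The concern.** The paragraph sets only one power level, .80, so a reader will take sufficient power to mean 80%. The number analysed after 15% loss is also fixed, at about 115 per arm. Level, power, allocation and sample size together determine the detectable standardized effect unless some variance reduction is assumed, and none is mentioned. The result is larger than 0.35.

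This matters because the detectable effect is the yardstick for reading a null result. The article describes 0.35 as in line with effects seen in other adherence interventions. If the trial finds no difference, readers will judge how far an effect of that size has been excluded, and they should have the figure that the design supports.

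**Working it through.** **Inputs.** Two-sided alpha 0.05, power 0.80, 115 per arm, 15% loss and target 270 (Sample Size); 1:1 allocation (Design). The effect size d is in standard deviation units.

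**The loss allowance reproduces.** 230 / 0.85 = 270.6, stated as 270. In reverse, 270 × 0.85 = 229.5, or about 115 per arm. So 115 per arm is the number that the 0.35 claim refers to.

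**Detectable effect at 115 per arm.** Normal approximation:

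d = (1.960 + 0.842) × √(2/115) = 2.802 × 0.1319 = 0.369.

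The t-test gives 0.371. Both round to 0.37.

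**Power at 0.35 with 115 per arm.** 0.35 / 0.1319 = 2.654, and Φ(2.654 − 1.960) = Φ(0.694) = 75.6%. The t-test gives 75.3%.

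**Number needed for 0.35.** n per arm = 2 × (2.802 / 0.35)² = 128.2, so 129 (normal); the t-test gives 129.1, so 130. That is 260 evaluable, and 260 / 270 = 96.3%, so at most 3.7% could be lost from 270. Under 15% loss, 260 / 0.85 = 306 would have to be enrolled.

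**Where 0.35 could come from.** Unadjusted, two-sided unless stated:

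| Analysed per arm | Situation | Power at 0.35 | Effect at 80% power |
|---|---|---|---|
| 115 | 15% loss | 75–76% | 0.37 |
| 121 | 10% loss | 77–78% | 0.36 |
| 124 | 8% loss | 78–79% | 0.36 |
| 135 | no loss | 82% | 0.34 |
| 115, one-sided | contrary to the text | 84% | 0.33 |

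Even at the expected 8% to 10% loss, the unadjusted figure stays just under 80%.

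**Effect of using baseline.** The article gives no correlation r, so these values are assumptions. Adjusting for baseline multiplies the variance by 1 − r²; a change score multiplies it by 2(1 − r). At 115 per arm and d = 0.35 (normal approximation):

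| r | Baseline-adjusted | Change score |
|---|---|---|
| 0.3 | 79.5% | 61.1% |
| 0.4 | 82.5% | 67.8% |
| 0.5 | 86.5% | 75.6% |
| 0.6 | 91.3% | 84.3% |

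The adjusted analysis reaches 80% when √(1 − r²) = 0.35 / 0.369, so r = 0.32. With the t-test value 0.371, r = 0.33. A correlation of about 0.34 or more is enough under either. A change score needs r above 0.5 to gain anything over the unadjusted comparison.

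**The 4% increase.** It cannot settle the matter, because no standard deviation is given. At d = 0.369 it implies 4 / 0.369 = 10.8 percentage points; at d = 0.35 it implies 4 / 0.35 = 11.4.

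**The case against.** The strongest reply is that the trial does not plan an unadjusted comparison at a single time. The Statistical Analyses section expects a mixed model that uses within-person correlation, adds covariates for precision, and commits to using baseline values in one form or another. A baseline correlation in the mid 0.30s is a modest requirement. Averaging two follow-ups would also lift power at 0.35 to between 82% and 91% for correlations from 0.7 down to 0.3. Moreover, the 0.35 sentence attaches no number to sufficient power.

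Much of this stands. It rules out saying that the trial lacks power for 0.35; the planned analysis may well provide it. It does not make the printed figure follow from the printed inputs. No variance reduction is stated, and the gain is not automatic: change scores remain an option, and below a correlation of 0.5 they lose power. Entry is restricted to patients reporting inadequate adherence, which tends to weaken the correlation with baseline. The gain from averaging also depends on how far a comparison focused on one year draws on earlier visits. As for sufficient power, .80 is the only level the section offers.

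Two stronger readings are tempting. Neither is supported:

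- **Power at 0.2.** A reader might infer a claim of 80% power down to 0.2 from "Power for this type of trial should be sufficient to identify small to moderate effects", since that category is defined as 0.2 to 0.5. Power at 0.2 with 115 per arm is indeed only 33%. But the sentence speaks generally of this kind of trial, and the next one gives this trial's own figure, 0.35. The 33% contradicts nothing that is stated.
- **Binary process outcomes.** A reader might take "We will have more than sufficient power to detect differences in those outcomes" to be wrong as well. It states no base rate and no difference, so there is nothing to recompute. The detectable difference depends on the rate assumed: at 115 per arm and 80% power it is about 9 points from a base rate of 2%, 14 from 10%, 18 from 50% and 8.5 from 90%. No single range can be put in its place.

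**Conclusion.** The 0.35 figure is wrong as written, by a small amount. With two-sided alpha 0.05, 1:1 allocation, 115 evaluable per arm and no variance reduction, the effect detectable with 80% power is 0.37, and power at 0.35 is about 75%. The shortfall is 0.02 in effect size, or 4.4 to 4.7 points of power.

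The finding rests on reading sufficient power as .80 and on the absence of any stated correlation or repeated-measures gain. It is a minor error in a reported design figure. It does not show that the trial is underpowered for 0.35 under its planned analysis, and the enrollment target itself is consistent with the 115 per arm it was built on.

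**What to change.** Change the 0.35 sentence in the Sample Size section in one of two ways:

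1. State that, with 230 evaluable patients, the trial has 80% power for an effect size of 0.37 and about 75% for 0.35.
2. Keep 0.35, and state that it relies on a baseline-adjusted analysis with an assumed baseline to follow-up correlation of about 0.34 or more. The main analysis should then be fixed as baseline adjustment, because a change score does not give the same gain at that correlation.

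Whichever is chosen should be carried into the report of results, where the detectable effect will be used to interpret the estimate. The cost is text only. The abstract says enrollment was completed in 2015, and the change needs no further patients and no new data. The general sentence on small to moderate effects and the sentence on binary outcomes need no correction on this account.

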#### Trial Registration, Ethics, Consent, and Institutional Review Board Approval

This trial is registered in clinicaltrials.gov (NCT01505660) and received approval from UW Human Subjects Division (UW #41128). Informed consent to participate in the study was obtained from each participant. They are not pressured to participate and participation or not does not impact their ability to receive care at the clinic.

## Discussion

### Design

The key consideration in designing this trial was to adapt and test an evidence-based model of collaborative care [50] to enhance ARV adherence. We used existing clinical staff members in a manner that is streamlined and could be integrated into care. The intervention offers patients and health care delivery teams resources necessary to increase the use of evidence-based treatments to improve adherence, depression, and substance use. The case manager-based collaborative model is a system of care that can be integrated into clinical care settings to provide patient-centered care. The intervention was modeled on the PEARLS and PATHWAYS studies [50,51] based on the IMPACT study [57]. We made modifications to focus on adherence and care for PLWH and to ensure that the interventions were sufficiently streamlined to facilitate use in routine care.

### Stepped-Care Approach

We are using a stepped-care approach allowing intervention intensity to be tailored to the patient’s needs [101]. Earlier depression studies suggested incorporating additional interventions led to improvements and sustainability beyond that obtained by telephone care management alone [102-104]. Similarly, adherence studies have demonstrated a greater impact with added services targeting those with the highest needs [45]. This stepped-care approach allows us to target these interventions to those at greatest need and who are most likely to benefit rather than on everyone to maintain feasibility for incorporating into busy clinical care settings.

### Telephone

While many care management protocols incorporate community outreach and home visits, these are not likely applicable to HIV care in the current funding environment. However, telephone-based care management approaches [53,54,104-107] have shown improvements in readmission rates and depression levels. Therefore, we included a brief telephone-based approach for the initial interactions (2 and 6 weeks), as well as later check-ins for those doing well, to enhance feasibility.

### Intensity

We designed the intervention to be less intensive than previous care management trials [50,51,63] to enhance feasibility in clinical practice. Prior care management approaches often included home visits and frequent, hour-long sessions for everyone in the intervention group. We truncated these practices and are using phone-based check-in calls, and office- or phone-based visits for PST targeted to those with the greatest need. An advantage of using case managers to deliver the intervention is the ability to leverage existing patient-case manager relationships.

### Adherence Measurement

Patients with inadequate medication adherence measured by the 14-day adherence item are eligible for inclusion. Although self-reported adherence has been critiqued for inaccuracies, these concerns have centered on over-reporting rather than under-reporting of adherence. Patients who report poor adherence are likely to truly have poor adherence. We chose the 14-day timeframe to include weekends, which are frequent times of missed doses and avoided longer time frames to limit recall errors and focus on current behavior.

### Limitations

This intervention is being evaluated in English-speaking patients only. A Spanish language version of the clinical assessment is now offered at the UW HIV clinic, and an Amharic version has just been introduced. Another limitation is it includes only one clinic. Additional studies will be needed at other sites and in non-English speaking patients to determine if findings are generalizable. While we track the number of call attempts (successful and unsuccessful) and other contributions to staff time burden, our focus is not specifically on evaluating costs. The use of self-reported adherence as one of the primary outcomes may be considered a limitation. We have previously demonstrated high correlations between self-reported adherence and viral load, pharmacy refill data, and unannounced pill count data [108,109]. Furthermore, self-reported adherence data has been shown not to inflate effects of adherence interventions [44]. Self-reported adherence is one of several outcomes. We collect adherence in the clinical assessment from all patients as part of care as opposed to just in the intervention itself, reducing the likelihood of biased responses from those in the intervention group. The clinical assessment includes a normalizing statement, and we selected an intermediate timeframe to minimize concerns with recall bias. A prior meta-analysis has demonstrated that the ability to identify existing intervention effects are stronger when using adherence measures with longer recall periods (2 weeks or 1 month rather than 7 days or shorter) [44].

Another potential limitation is that providers and case managers can have patients in both usual care and intervention arms, and therefore may be subject to spillover effects, which could dilute the impact detected. Systematic changes such as automated email reminders of time to contact patients are not subject to spillover. Concern about spillover effects is one of the factors that led some investigators to evaluate nonintegrated approaches for delivering interventions. However, given the potential advantages of having a care manager with an established relationship with the patient, as well as designing an intervention that would be feasible within clinical care settings, we elected to conduct this intervention using existing clinic case management staff despite the potential for spillover effects. While this does not allow feasible blinding, the outcomes are assessed as part of routine care and not part of the trial.

Finally, the intervention is a comprehensive multifaceted approach, so we may be unable to isolate the critical factors necessary for success.

### Strengths

A key strength is the adaption of an evidenced-based collaborative care intervention for use among PLWH with inadequate adherence. A collaborative care approach has long been recommended for improving adherence [110], as has a stepped-care approach targeting patients with particular difficulty to receive more intensive strategies [110]. We are attempting to maximize generalizability by conducting this study among a clinical care patient population. We identify patients from the clinical assessment given to the entire clinic population as part of routine care. This approach contrasts with the subset of patients who return mail-in surveys, which has often been the recruitment strategy for other care management studies. In particular, we do not exclude patients with substance abuse or depression. In fact, these two inter-related problems are key contributors to inadequate adherence in clinical care, and therefore this intervention addresses all three rather than focusing on inadequate adherence in isolation. Another strength is using care managers who are routinely part of HIV care settings as this makes it much more likely to be feasible for widespread use.

We integrated proactive telephone check-ins. There is considerable support for the efficacy of telephone-based interventions with a number of health problems in various patient populations [111]. Among PLWH, recent studies have focused on sexual risk reduction [112], interpersonal therapy for rural PLWH with depression [113], tobacco cessation [114], and adherence [115]. Potential advantages of telephone-based strategies include cost effectiveness and reducing barriers to care [116]. We optimized resource allocation by combining routine telephone check-ins with in-clinic, in-person PST for those who need a more intensive intervention.

Finally, using a Web-based PRO platform for data collection enhances fidelity, and allows automation of reminders to case managers and a more proactive systematized approach to routine follow-up.

### Conclusion

Medication adherence is critically important for long-term outcomes among PLWH. There is a need to identify best practices for implementing evidence-based collaborative care models that are effective and feasible in clinical care. Adherence efficacy trials have not led to sufficient improvements, and there remains little guidance regarding how adherence interventions should be implemented into clinical care. By focusing on improving adherence within care settings using existing staff, routine assessment of key domains, such as depression, adherence, and substance use, and feasible interventions, we propose to evaluate this innovative way to improve clinical outcomes.

## Abbreviations

ARVs: antiretroviral medications
EHR: electronic health records
HIV: human immunodeficiency virus
IRT: item response theory
PEARLS: Program to Encourage Active, Rewarding Lives study
PHQ-9: Patient’s Health Questionnaire
PLWH: persons living with HIV
PROs: patient-reported outcomes
PST: problem solving therapy
RCT: randomized controlled trial
UW: University of Washington
UW HIV: University of Washington Harborview Madison HIV
VL: viral load
